## Preliminary results

By mid-March 2020 29,516 of the potential study participants received at least an invitation letter and at least one reminder. Overall, 4719 mothers and 889 fathers completed the screening step 1. Three participants were adoptive parents and three participants did indicate to be other caregivers (for example stepparents). So far, either the mother or the father or both parents of 4866 children (16.5%) have completed the screening step 1 questionnaire. All persons gave their informed consent prior to their inclusion in the study.

4472 participants came from Berlin, 75 from Flensburg, 933 from Leipzig and the remaining participants were living elsewhere at the time of the screening step 1. 811 participants were younger than 30 years, 4779 between 30 and 49 years and 21 participants 50 years or older (three values missing). 860 participants did indicate to be born outside Germany, 272 to be single parents and 2351 participants having more than one child.

Overall, 1139 mothers (24.1%) and 154 fathers (17.3%) screened so far “positive” in the screening step 1. As described above, only mothers with a “positive” screening step 1 are invited to the screening step 2.

## Discussion

This is the first study in Germany using a large population-based random sample from local registry offices to assess psychosocial stress and mental health disorders in parents and their children in early childhood. We chose a cohort design for the present study to assess longitudinal data after birth and to have a look at how psychosocial stress and mental health disorders are developing over a 6 month observation period.

### Strengths and potential limitations

It is important to detect parents with an elevated stress level at a very early stage, to plan preventive strategies to reduce the risk for developing mental health disorders in both parents and children. We developed a short screening instrument for psychosocial stress in early childhood. It includes known relevant stressors associated with postnatal mental health disorders and should be helpful to identify vulnerable parents and their children in the future. The simple screening questionnaire is accessible online and can be filled out by the invited parents (estimated time 10–15 min). We discussed the questionnaires with experts from a multidisciplinary background and adapted them after a piloting phase.

For the screening step 2, we needed instruments to assess the predefined outcomes in mothers under risk as well as in their children. To assess the occurrence of mental health disorders a psychiatric interview is considered the gold standard. We, therefore, decided to use an adapted version of the MINI [59], because it is a short structured and validated interview. A recent study from Sweden investigated the acceptability of the MINI in a primary care setting and concluded that the MINI interview was well accepted by patients and general practitioners [69]. Using the MINI not only occurrence rates of postnatal depression or anxiety, but also the occurrence of other mental health disorders—like obsessive–compulsive disorders or eating disorders—will be assessed. This will add more information regarding these mental health disorders in mothers with children in the early childhood period. One limitation of the MINI is that it is a complex interview. The interviewers in our study will, therefore, receive an extensive training before performing interviews for the screening step 2. Another limitation is that a psychiatric interview may be potentially distressing for participants who until that moment may not have had any contact with psychiatric assessments. A sensitive introduction to the interview is, therefore, essential and part of the interviewer training. The additional assessment of EPDS scores will allow us to compare our study with data from other international studies and to assess mild depressive symptoms that do not meet the diagnostic criteria for major depression disorder. Using the EPDS Scores, we will also observe how depressive symptoms are developing over the 6 month observation period.

For the assessment of symptoms of regulatory problems of the child, we will use the questionnaire on crying, feeding and sleeping disorders [60], which is the only self-reported questionnaire currently available for this kind of problems. We expect that mothers with an elevated stress level or a mental health disorder may report more often that their children are showing signs of regulatory problems. Therefore, the occurrence of this kind of problems may be over-estimated, because we have only information based on the information of the mother. We also decided to evaluate the rather new hypothetical construct of parental burnout and we will use a specific questionnaire that is currently being tested in different countries and different languages worldwide (The International Investigation of Parental Burnout [12]).

Besides assessing epidemiological data, we are interested in analyzing the actual health care and social service utilization for this understudied subpopulation in Germany. For this purpose, we developed a questionnaire containing questions regarding health care and social services utilization of the participating families. The knowledge of specific utilisation behaviour by different subgroups may help to better address health care and social services needs in the future. We would expect that the variety of available services is complex and that it may discourage particularly less educated parents from making use of it.

One limitation of our study is the generalizability of our sample, which is coming from only three registry offices. Our results may be considered representative for these regions but not for the rest of Germany, especially not for rural areas. All recruitment regions are urban areas of different size including regions from Northern as well as Eastern Germany. The participants may be possibly considered as being representative for these regions to some extent, but certainly not for the rest of Germany. Interpreting the statistical results, we will carefully evaluate possible types of bias including sampling bias considering our recruitment strategy.

We decided to invite only parents with children already born to participate in this study (instead of inviting women while still pregnant). Otherwise, we would not have been able to use the registry offices for sampling. Using this approach, we hope to reach as many participants as possible in the respective regions. However, we know that we will have limited information on some risk factors during pregnancy. We decided to evaluate only mothers and their children in the screening step 2, because mothers are usually the main reference persons of the children in the first years of life. However, future studies should consider assessing more information about fathers and their special situation and needs within the first years after birth. We excluded participants under 18 years due to ethical and organisational reasons, such as acquiring written informed consents of their parents as well, i.e., the grandparents of the index child. Study participation might be lower among parents with lower educational levels as compared to higher educational levels, as seen in many other studies [70–73]. Therefore, we are expecting an underrepresentation of socially disadvantaged parents in our study population. Where possible, we adapted the study documents keeping them as short as possible and using simple language to decrease the selection bias. On the other hand, potential participants are much more likely to take part in a study when the subject is salient to the participants’ life [73], which we expect for our observational cohort study.

Our hypothesis is that mothers with an elevated level of psychosocial stress are often showing mental health symptoms. In addition, we expect that their children are showing signs of regulatory problems. If we are looking at patterns, we expect to find the mental health problems to remain relatively stable if the mothers or children are not receiving support – for example by social and health care institutions. And we expect to replicate already known determinants of mental health problems as well as further possible factors.

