## Rationale

Psychosocial stress in parents with young children is not only a burden for their own mental health but may also negatively affect the children’s short and long-term mental well-being [1]. Epidemiological studies on maternal mental health disorders in the postnatal period have been almost exclusively focused on postnatal depression and anxiety disorders [2–4]. For postnatal depression, prevalence estimates revealed large variations worldwide [3, 4]. A meta-analysis based only on studies using the Edinburgh Postnatal Depression Scale (EPDS)—a self-report screening instrument for postnatal depression [5]—assessed a global prevalence of almost 18% [4]. An international review including also studies using psychiatric interviews revealed prevalences ranging from 4 to 64% [3]. According to another systematic review, the prevalence of self-reported postnatal anxiety symptoms was 15% and of clinically diagnosed anxiety disorders around 10% [2]. The few German studies assessing prevalence data on postnatal maternal mental health disorders revealed estimates between 3 and 6% for postnatal depression and around 11% for postnatal anxiety [6–8]. Ongoing research is focusing especially on postnatal depression or anxiety disorders, but there are less studies assessing prevalence data of other postnatal mental health problems like obsessive–compulsive disorders [9, 10] or parental burnout, a concept that has only recently been suggested and investigated [11, 12]. One of the few studies in this field reported that 10.4% of the parents with at least one child at home belonged to an average parental burnout category and 2.1% of the parents to a high parental burnout category, but the sample included parents with children of all ages [13].

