**Fig. 1 Fig1:**
[figure not shown]
Flowchart SKKIPPI Cohort Study

While both mothers and fathers can participate in the first step, for the second step, only mothers will be included. As mothers are usually the main reference persons of the children in the first years of life, a significantly higher participation of them is expected. For this reason, we decided to assess mental health problems only in mothers and their children. Mothers who screened “positive” in the first step, meaning achieved at least 10 points in the online questionnaire, will enter the second step of the screening for a more in-depth assessment, where specially trained study staff will conduct phone interviews for mental health disorders (adapted version from the MINI [59]). In addition, questions on depressive symptoms, symptoms of parental burnout, symptoms of regulatory problems of the children, questions on childhood trauma of the parents, and detailed data on kind and frequency of health and social care utilisation will be collected (via telephone interview or online questionnaire).

After 6 months, a follow-up assessment will be performed with all mothers with a current mental health disorder (based on the MINI interview [59]) or a positive outcome in the Edinburgh Postnatal Depression Scale (EPDS) [5] or Parental Burnout Assessment questionnaire (PBA) [12] within the screening step 2 (“positive” screening step 2). The same data as in the screening step 2 stage will be collected, with additional data about the use of health care services and official support services in the last 6 months. We estimated that 80% of the participants would take part in the follow-up assessment.

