In addition, questions on sociodemographic characteristics, stress related to relationships, family and work, lack of social support and critical life events related to the pregnancy and child (for example an unplanned pregnancy or severe illness of the child) will be assessed. To reduce selection bias, the questionnaire was kept as long as necessary but as short as possible and in simple language, to achieve a high participation rate especially in those with a lower educational level or non-native German speakers. Otherwise, particularly those at risk for psychosocial stress and mental health disorders might be under-represented in the study. Therefore, either short questionnaires such as the Patient Health Questionnaire 4 [63] or individual questions from existing questionnaires were selected or adapted (the Crying, Feeding, Sleeping Questionnaire [60], the Zohar-Fineberg Obsessive Compulsive Screen [64], the Postpartum Bonding questionnaire [65], and the KID 0–3 questionnaire [66]). We developed a scoring system with points ranging from 0–5 for each question. The scores were discussed with a panel of experts from psychology, paediatrics, health sciences, and data sciences, taken into account cut-offs of included questionnaires. We piloted the questionnaire and adapted it as indicated (e.g. adding or rewording of response options). The scope of this pilot study was to test if the questionnaire was comprehensible, appropriate and feasible for the participants. Cut-offs were defined consensus based in order to identify a maximum of mothers with possible disorders, but the data from pilot study did not allow to conduct an in-depth analysis to calculate sensitivity or specificity. All mothers with an elevated score are invited to the screening step 2. This score was adjusted later on because the results of the first participants showed that too many mothers were included in the screening step 2 showing no current mental health problems. To increase the response among the major groups of parents with a migration background, all study documents of the screening step 1 were translated to English, Turkish, and Arabic.

#### Screening step 2

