The screening step 2 (Table 1) includes the following questionnaires:Adapted version of the M.I.N.I. Version 7.02, a structured interview based on DSM-V and ICD-10 [59]. Suicidal and psychotic symptoms will only be assessed using an abbreviated version and are, therefore, not diagnostically interpretable. Modules on antisocial personality disorder and bipolar disorders were not considered, but major depressive episodes and manic/hypomanic episodes will be assessed separately.Parental Burnout Assessment (PBA) [12].Questionnaire on crying, feeding and sleeping disorders [60].Edinburgh Postnatal Depression Scale (EPDS) [5, 67].Questions on childhood trauma of parents [66].Questionnaires on the use of health care and psychosocial services (self-developed).

**Table 1 Tab1:** Screening steps and instruments

Screening step	Instrument
Screening step 1	Self-developed questionnaire on parental psychosocial stress symptoms and signs of regulatory problems in the children
Screening step 2	MINI [59]
Screening step 2	Parental burnout assessment [12]
Screening step 2	Edinburgh postnatal depression scale [5, 67]
Screening step	Questionnaire on crying, feeding and sleeping [60]
Screening step 2	Questions on childhood trauma of the parents [66]
Screening step 2	Self-developed questionnaire on health care and psychosocial service utilization

All interviewers will receive an intensive training based on Standard Operating Procedures (SOP). This training is focusing especially on the acquisition of interviews techniques to assess accurately mental health disorders using the M.I.N.I. interview [59]. After the formal training, each interviewer will do test interviews for several weeks under continuous supervision. Regular supervision of the interviewers will take place.

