### Statistical analysis

In the three recruitment areas of the cohort study (Berlin, Leipzig and Flensburg) almost 49,000 children have been born annually in recent years. A random sample of 30,000 children is drawn by the residents' registration offices, and their parents are invited to take part in the study. The response is estimated to be 20%; therefore, about 6000 mother–child pairs are expected to participate in the study. Assuming a prevalence of mental health problems in postnatal mothers of about 20% [8], a similar prevalence of regulatory problems in their children [68] and a considerable overlap of both problems, about 1,500 of the estimated 6,000 mother–child-pairs are expected to be included into the screening step 2 (Fig. 1). In the screening step 2, we estimate that about 1,200 participating mother–child-pairs with maternal mental health disorders and/or symptoms of regulatory problems in the child will be identified. For an occurrence of 20% of mental health disorders (1200 of 6000), a two-sided exact Clopper-Pearson 95%-confidence interval (95% CI) of 6000 participants has a width of ± 1% (i.e., 95% CI [19%; 21%]). This is considered sufficiently precise.

All data will be analysed descriptively. Results are presented in the form of means, standard deviations, medians and quartiles for continuous data, and frequencies and percentages for categorical data. Results (including occurrences) are reported with two-sided 95% CIs. Influencing factors for the presence of psychosocial stress or mental health disorders are analysed using logistic regression yielding odds ratios (OR) with 95% CIs and *p* values. Influencing factors or group comparisons for continuous variables (e.g. costs) will be analysed by linear regression or analysis of covariance (ANCOVA), yielding regression coefficients or means with 95% CIs and *p* values. All CIs and *p* values are two-sided and are interpreted exploratively (there is no formal significance level). Missing values are not replaced. All analyses are carried out with the respective available data (full analysis set).

For the cost analysis, the monetary valuation of the utilization of services is carried out by multiplying the frequency of utilization and corresponding standardized cost rates.

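### The EPDS is given only to screen-positive mothers, so the unqualified promise of comparison with international studies is not supported by the design

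*Protocol article*

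**What the plan says.** - **The claim.** Protocol article, Discussion, Strengths and potential limitations: "The additional assessment of EPDS scores will allow us to compare our study with data from other international studies". No limit is attached to this sentence.
- **Where the EPDS is given.** Methods, Instruments, lists it under screening step 2 (also in Table 1). Under Procedures it also serves the 6-month follow-up of mothers who were positive in step 2.
- **Who reaches step 2.** Procedures: mothers who screen positive, "meaning achieved at least 10 points in the online questionnaire, will enter the second step of the screening". Preliminary results repeats that only positive mothers "are invited to the screening step 2" and counts 1,139 of 4,719 (24.1%). No EPDS in screen-negative mothers, or in a sample of them, is described.
- **What the step-1 score contains.** Instruments, Screening step 1: symptoms of depression and anxiety, other mental health items, child regulatory signs, stressors and life events.
- **How well the screen works.** The same section says that the pilot could not yield sensitivity or specificity. It also says that the cut-off was adjusted after the first participants, because too many mothers without current problems reached step 2.
- **Role of the EPDS.** Endpoints makes depressive symptoms by EPDS (10–12 minor, 13 or more major) a primary endpoint.
- **External EPDS figure.** Rationale cites a meta-analysis of EPDS studies that "assessed a global prevalence of almost 18" per cent.

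**The concern.** Mothers are selected for the EPDS partly on the symptoms that the EPDS measures. An EPDS proportion or mean among step-2 mothers is therefore raised by selection when set beside a sample of unselected mothers. Dividing the step-2 positives by all step-1 mothers removes that inflation, but it counts every mother below the step-1 cut-off as scoring 0–9 on the EPDS. That is right only if the screen misses nobody.

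The limitations in the Discussion cover region, response, social selection and maternal over-reporting, but not this gate. A reader would take international comparability of depressive symptoms as a strength of the study. A published EPDS percentage placed next to an international prevalence could then mislead in either direction, depending on the denominator chosen.

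**Working it through.** **The plan's own figures.** Statistical analysis and Preliminary results reproduce:
- 30,000 × 0.20 = 6,000 pairs.
- Planned step-2 share: 1,500/6,000 = 25%.
- 1,200/6,000 = 20%, with an exact Clopper-Pearson 95% CI of 18.99% to 21.03%, stated as 19% to 21%. This calculation divides cases found in step 2 by all step-1 participants.
- Observed step-1 positive share in mothers: 1,139/4,719 = 24.1%. So 4,719 − 1,139 = 3,580 mothers (75.9%) get no EPDS.

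**Inputs for the check.**
- S = 1,139/4,719 = 0.2414 (Preliminary results).
- p = true EPDS-positive share among step-1 mothers. It is set to 0.18 for illustration, the order of the figure in the Rationale. The plan does not name this figure as the one to compare with.
- s = sensitivity of the step-1 screen for EPDS-positive mothers. The document gives none; values from 1.0 to 0.5 are assumed.
- Full step-2 participation is assumed at first.

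**Formulas.**
- Share among step-2 mothers = p × s / S
- Share over all step-1 mothers = p × s
- Share among the unassessed screen-negatives = p × (1 − s) / (1 − S)

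| Assumed s | Among step-2 mothers | Over all step-1 mothers | Among screen-negatives |
|---|---|---|---|
| 1.0 | 0.18/0.2414 = 74.6% | 18.0% | 0% |
| 0.8 | 0.144/0.2414 = 59.7% | 14.4% | 0.036/0.7586 = 4.7% |
| 0.5 | 0.09/0.2414 = 37.3% | 9.0% | 0.09/0.7586 = 11.9% |

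With the planned S of 25% the step-2 column becomes 72%, 57.6% and 36%, so the result does not hinge on the interim count.

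**Reading the table.** The step-2 share is about 2 to 4 times the true value. The all-mothers share equals it only at s = 1. Each percentage point of EPDS positivity among screen-negatives adds 0.76 points to the true share, and the described design cannot observe it.

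**Step-2 participation.** If a fraction r of the invited mothers completes the EPDS, independently of EPDS status, the all-mothers share falls to p × s × r. With s = 0.8 and r = 0.8 (both assumed) it is 0.18 × 0.8 × 0.8 = 11.5%.

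**The case against.** The strongest reply has four parts.

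1. **A usable figure does exist.** A reader might infer that no comparable EPDS figure can come out of this study. The document does not support that. The article's own calculation puts step-2 cases over all step-1 participants. Applied to the EPDS, this gives a lower bound, close to the truth if sensitivity and step-2 participation are high. High sensitivity was the stated aim of the questionnaire. This stands: comparability is unproven, not impossible. But the aim was not verified, and the reason given for changing the cut-off suggests a stricter threshold, which cannot raise sensitivity.

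2. **It is one Discussion sentence, and it names neither a prevalence comparison nor the 18%.** True, so the 18% is used here only as an illustration. The sentence still states a property of the study without limit, and it concerns a primary endpoint. The article's general promise to evaluate bias refers to the recruitment strategy and does not reach the step-1 gate.

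3. **The PHQ-4.** A reader might infer that a ready full-sample measure is being wrongly ignored and should replace the EPDS. The article says that short questionnaires or single items were selected or adapted, and that response options were changed after piloting. It does not establish that the PHQ-4 was kept intact. It also says that all data will be described, so the absence of a named PHQ-4 table is silence in a condensed article. A PHQ-4 result is in any case not an EPDS result.

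4. **Mild symptoms.** It may seem that the 10–12 band is what the screen loses most. That is plausible but cannot be derived, because stress, family and child items can also bring a mildly depressed mother to 10 points.

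**Conclusion.** The comparability statement is wrong as written, because it attributes to the EPDS data a property that the described design does not secure. For an assumed true share of 18%, full step-2 participation and sensitivities of 1.0, 0.8 and 0.5, the step-2 share would be about 75%, 60% and 37%, and the all-mothers share 18%, 14.4% and 9%. The two series have different denominators, so they should be compared at the same sensitivity and not run together into one range. At perfect sensitivity and full participation the all-mothers figure would be correct.

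The size rests on assumed sensitivities and an illustrative prevalence. The direction does not: selection on a score that contains depression items raises the step-2 share, and treating unassessed mothers as negative can only lower the all-mothers share. Nothing here argues for dropping the EPDS as an occurrence endpoint.

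**What to change.** Keep the EPDS endpoint and qualify the sentence in Strengths and potential limitations:
- Label step-2 EPDS results as applying to screen-positive mothers only.
- Report any EPDS share over all step-1 mothers as a lower bound, with a range over assumed screen sensitivity and step-2 participation.
- Do not set either figure beside EPDS prevalences from unselected samples as like for like.
- If the PHQ-4 items were used unaltered in step 1, also report their standard-scored proportions in all step-1 mothers, and separately in fathers. Present this as a separate comparison with PHQ-4 studies, not as a substitute for an EPDS figure.

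None of this needs new data. The cost is a less favourable comparability statement and one extra table. If recruitment still allows, giving the EPDS to a random sample of screen-negative mothers and weighting the results would support the comparison directly, but that does mean extra data collection.

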### Instruments

#### Screening step 1

In the screening step 1, study participants fill out a short online-questionnaire. The questionnaire was developed with the aim of having a high sensitivity to detect potential mental health disorders and psychosocial stress. By implementing a two-step screening design we hope to reach a high sensitivity and high specificity, allowing an accurate early detection of stress or mental health problems in parents and their children. There are existing screening instruments like the Babylotse-Plus screening form [61] or the Heidelberg Stress scale [62], but they showed either a high sensitivity and low specificity [61] or only a moderate sensitivity [62].

The questionnaire for the screening step 1 (self-developed and adapted parts) contains questions regarding the parent’s health status: symptoms of depression and/or anxiety, obsessive–compulsive problems, abuse/addiction to alcohol/drugs, eating problems, lack of impulse control or mood swings, pre-existing mental health disorders. Questions regarding the child include the assessment of signs of crying, sleeping or feeding problems.

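### The expectation that stressed mothers often show mental health symptoms is partly built into the screening score, and step-2 data alone cannot show that stress and symptoms are associated

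*Protocol article*

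**What the plan says.** All references are to the protocol article.

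- **The expectation.** Under Strengths and potential limitations: "Our hypothesis is that mothers with an elevated level of psychosocial stress are often showing mental health symptoms".
- **What counts as elevated stress.** The Abstract says that mothers with signs of psychosocial stress go on to interview. The Discussion describes the step-1 questionnaire thus: "We developed a short screening instrument for psychosocial stress in early childhood". Under Procedures the entry rule is: "Mothers who screened “positive” in the first step, meaning achieved at least 10 points in the online questionnaire, will enter the second step". No other definition of elevated stress is given.
- **What the questionnaire contains.** Under Instruments, Screening step 1, the parental health items are "symptoms of depression and/or anxiety, obsessive–compulsive problems, abuse/addiction to alcohol/drugs, eating problems, lack of impulse control or mood swings, pre-existing mental health disorders". The same instrument covers "stress related to relationships, family and work, lack of social support and critical life events related to the pregnancy and child", and signs of crying, sleeping or feeding problems in the child. Each question earns 0 to 5 points. Separate symptom and stress scores are not described.
- **The threshold.** The same section reports that the score was adjusted after the first participants, because step 2 was taking in too many mothers without a current mental health problem.
- **Where the endpoint instruments are used.** MINI, EPDS and PBA belong to screening step 2 (Table 1) and supply all three maternal primary endpoints.
- **Analysis.** Under Statistical analysis, logistic regression is planned for factors influencing stress or mental health disorders. It is exploratory, uses the available data and names no population. Endpoints lists family, work and life-event stressors among the potential risk factors, but no step-1 symptom endpoint.

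**The concern.** The exposure in the stated expectation is elevated stress and the outcome is mental health symptoms. The measure of the exposure contains the outcome: a mother can reach 10 points partly or largely through symptom items. Finding many symptoms among mothers above the cut-off is then in part a property of the score. The later change of the cut-off adds to this, because the boundary of a positive screen was moved in the light of how many step-2 mothers had problems.

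No mother below the cut-off has a MINI, EPDS or PBA result, so the step-2 proportion has nothing to be compared with on those instruments. Relating individual stressors to those outcomes within step 2 does not solve this. Among mothers selected on a sum, those with few stress points need more points from elsewhere, which includes symptoms. That pushes the stressor–symptom association downwards and can reverse its sign.

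At stake is whether the study can say anything about the first expectation it states, and whether step-2 stressor associations are read at face value.

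**Working it through.** **1. The document's own figures.**
- Precision (Statistical analysis): exact Clopper–Pearson interval for 1200/6000 = 18.99% to 21.03%. This reproduces the stated ±1%, but it concerns occurrence, not a stress–symptom association.
- Screen-positive mothers (Preliminary results): 1139/4719 = 24.1%, as stated.

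**2. Mothers without any endpoint instrument.**
- So far: 4719 − 1139 = 3580.
- As planned: 6000 − 1500 = 4500.

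**3. How much could be built in?** The scoring key is not shown, so this is a simulation under assumptions.
- Stress score *a* and symptom score *b* are standard normal with correlation ρ.
- Total *s* = (1 − *w*)·*a* + *w*·*b*, where *w* is the weight of the symptom items.
- Screen-positive = top 24.1% of *s*; symptomatic = top 20% of *b*; high stress = top 24.1% of *a*.
- 2,000,000 simulated mothers per setting.

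| ρ | *w* | Symptomatic, screen-positive | Symptomatic, screen-negative | Stress–symptom OR, all mothers | OR within screen-positives |
|---|---|---|---|---|---|
| 0 | 0.25 | 32.7% | 16.0% | 1.01 | 0.10 |
| 0 | 0.50 | 53.0% | 9.5% | 1.00 | 0.11 |
| 0 | 0.75 | 74.3% | 2.7% | 1.00 | 0.16 |
| 0.3 | 0.25 | 43.9% | 12.4% | 2.41 | 0.12 |
| 0.3 | 0.50 | 60.1% | 7.3% | 2.43 | 0.13 |
| 0.3 | 0.75 | 76.0% | 2.2% | 2.41 | 0.21 |
| 0.5 | 0.25 | 52.1% | 9.8% | 4.58 | 0.13 |
| 0.5 | 0.50 | 65.1% | 5.7% | 4.61 | 0.17 |
| 0.5 | 0.75 | 77.7% | 1.7% | 4.60 | 0.28 |

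With no association at all (ρ = 0), screen-positives still show far more symptoms than screen-negatives. With a true OR of about 2.4 (ρ = 0.3), the OR within screen-positives lies on the wrong side of 1.

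These sizes illustrate the mechanism and are not estimates for this study. The simulated outcome is the same symptom score that enters the sum. MINI, EPDS and PBA are separate measurements and the real score has further items, so the real distortion should be weaker.

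**4. Would a step-1 analysis be precise enough?** Assumed: two-sided 5%, 80% power (the document sets neither), and the top 25% on the stress items called high-stress.

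| Step-1 mothers | Symptom rate in the others | Smallest detectable difference | OR |
|---|---|---|---|
| 4719 | 10% | 3.0 points | 1.34 |
| 4719 | 20% | 3.9 points | 1.26 |
| 6000 | 10% | 2.7 points | 1.31 |
| 6000 | 20% | 3.5 points | 1.23 |

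For high-stress shares from 10% to 50%, the detectable OR runs from 1.19 to 1.51 across both sample sizes and both rates.

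**The case against.** The sentence is an informal expectation in the Discussion. It says that symptoms are frequent, names no comparator, and appears in neither the objectives nor the endpoints. The study is exploratory, with no formal significance level. Stressors are already planned as risk factors, and the choice of outcome, population and sub-score is detail that an article often leaves to the full protocol or analysis plan. All of this stands, and it makes the point one of interpretation and analysis, not an error in a stated figure.

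A reader might also infer four stronger things, which the document does not support:

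- **That the expectation cannot fail.** The reason given for adjusting the score shows that many early high scorers had no current problem. Points also come from stress and child items, and the item weights are not shown. The step-2 proportion can turn out low.
- **That there is no low-stress comparison at all.** This holds only for MINI, EPDS and PBA. Step 1 asks every mother about symptoms, including those below the cut-off, and the planned regression on available data does not exclude step 1.
- **That every parent completed an intact PHQ-4.** The text refers to "short questionnaires such as the Patient Health Questionnaire 4" among instruments or single questions that were chosen or adapted.
- **That the authors will present the step-2 proportion as proof.** No text says so.

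What the objection does not remove is the overlap. The only definition of elevated stress includes the symptoms it is expected to go with, and the article neither warns of this nor plans an analysis that keeps the two apart.

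**Conclusion.** The point holds in a limited form. The expectation is partly built in, because the score that defines elevated stress also counts symptoms and its threshold was adjusted in view of step-2 findings. The step-2 proportion may be high or low, but it cannot show that stress and symptoms are associated: 3,580 of 4,719 mothers so far (4,500 of 6,000 as planned) have no MINI, EPDS or PBA result. Stressor–symptom associations estimated within screen-positives alone are distorted by selection on the summed score and could change sign.

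How large the built-in part is cannot be read from the document. The conclusion assumes that the 10 points are reached by adding symptom and stress items, as the scoring description implies, and that no separate stress score exists.

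**What to change.** Keep symptom items and stress items apart in the analysis.

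1. In all step-1 mothers, and separately in fathers, regress self-reported depression and anxiety symptoms on the relationship, family, work, social-support and life-event items, singly or as a sub-score. Do not use the total score as the exposure.
2. As outcome, use the PHQ-4 at its published cut-off if it was administered intact. Otherwise use the adapted symptom items as a score.
3. Label the result an exploratory, cross-sectional association of self-reported symptoms.
4. Report MINI, EPDS and PBA proportions among screen-positives as description only, not as support for the expectation. State that stressor associations within step 2 are affected by the selection.

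This costs analysis wording and a short additional model; the data are already collected in step 1. The downside is that it addresses self-reported symptoms rather than diagnoses, and any stress sub-score would be unvalidated. A comparison on the diagnostic endpoints would need step-2 assessments in a random subsample of screen-negative mothers, which is new data collection and not part of this proposal.
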